## 1 Introduction

Kinesiology taping is a widely used therapeutic technique in rehabilitation, frequently applied to support musculoskeletal function, reduce pain, and enhance motor performance (1–3). Over the past decades, its clinical popularity has expanded across a wide range of conditions, from sports injuries to neurological disorders (2, 4).

Recently, interest has grown in exploring the potential of kinesiology taping beyond traditional musculoskeletal contexts, including its application in addressing complex neuromotor functions such as swallowing (5, 6).

Dysphagia is a frequent and often debilitating complication in individuals who have undergone neurosurgery for brain tumors. It may arise as a direct consequence of the tumor’s location and mass effect, or emerge postoperatively due to surgical trauma and neurological impairment (7, 8). Studies indicate that up to 47% of patients with brain tumors may require nasogastric tube feeding in the immediate postoperative period due to dysphagia (9). The incidence of dysphagia after neurosurgery may vary depending on the type of procedure performed, the extent of the surgery, the location of the tumor or lesion, and the patient’s overall health status. Nonetheless, studies suggest dysphagia is a relatively common complication after neurosurgery (10, 11). This condition not only compromises nutritional intake and increases the risk of aspiration pneumonia but also negatively impacts the overall quality of life and recovery trajectory in brain tumor survivors.

With significant advancements in surgery, chemotherapy, and radiotherapy, patients diagnosed with brain tumors now experience a higher survival rate (12–14). Consequently, it has become essential to focus on addressing any lingering neurological impairment and enhancing survivors’ quality of life (15, 16). In this sense, rehabilitation therapy has gained more attention as a valuable approach after brain tumor removal or reduction (15, 17). Furthermore, since stroke and brain tumors often result in comparable symptoms, such as cognitive, motor, and sensory dysfunctions, it is unsurprising that stroke and brain tumor survivors who performed similar rehabilitation programs achieve comparable outcomes (7, 18).

The use of kinesiology taping has generated positive results in a handful of early studies in rehabilitating dysphagia in stroke patients (5, 6, 19). In the pharyngeal phase of swallowing, the suprahyoid muscles are responsible for elevating and stabilizing the hyoid bone and larynx, contributing to proper swallowing mechanisms, including airway protection and opening of the upper esophageal sphincter. If the suprahyoid muscles are weak or damaged, it can result in dysphagia (20, 21). Therefore, strengthening the suprahyoid muscles can be essential to dysphagia rehabilitation to improve swallowing function and reduce the risk of complications (22). In addition, previous studies show that using kinesiology taping to strengthen the suprahyoid muscles can be an effective dysphagia rehabilitation intervention in stroke survivors (5, 6, 19). Thus, given these findings, we present the protocol of a combined intervention using dysphagia training and kinesiology tape application on brain tumor survivors. Therefore, this randomized controlled trial aims to assess the effects of kinesiology tape application in addition to usual care on dysphagia in brain tumor survivors after neurosurgery.

## 2 Methods

### 2.1 Design

This clinical trial is designed as a randomized controlled clinical trial, utilizing a 1:1 allocation ratio. All stages follow the Standard Protocol Items: Recommendations for Interventional Trials - SPIRIT reporting guidelines (23). The trial protocol has been registered with the Australian New Zealand Clinical Trials Registry (registration number: ACTRN12625001071415p).

### 2.2 Study setting

The study will be conducted in collaboration with a Hospital Centre in Portugal. The program will be delivered in the Neurosurgery Inpatient Unit.

### 2.3 Participants

Participants will be recruited from the Neurosurgery Inpatient Unit by the senior nurse manager, specialist in rehabilitation, and the neurologist/neurosurgeon.

Patients with dysphagia after brain tumor surgery will be included in this study if (a) diagnosis of oropharyngeal dysphagia, confirmed by flexible endoscopic evaluation of swallowing (FEES), (b) a Mini-Mental Status Examination (MMSE) score of 22 or higher, (c) ability to swallow voluntarily, (d) ability to swallow against resistance of tape, and (e) able to communicate with the investigator, to understand and comply with the study procedures.

Participants will be excluded if they have (a) dysphagia due to drug toxicity, (b) difficulty with or the inability to trigger a volitional swallow, (c) skin disorders, including allergies associated with taping attachment, (d) developed pneumonia or unstable medical conditions during the study, (e) presence of tracheotomy, (f) known history of progressive neurological disorder (for example, Parkinson’s disease, multiple sclerosis), (g) previously received swallowing therapy, (h) under 18 years of age, and (i) severe cognitive difficulties or significant active psychiatric disorders.

Any subjects who develop pneumonia or other unstable medical conditions at any point will be removed from the study and remanded to the best medical care.

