### 2.5 Randomization and blinding

Following baseline assessments, participants will be split into two groups: an experimental group and a control group. The randomization plan, including allocation groups and follow-up measurements (as shown in Figure 1), will be generated using online software that employs a random block sizes method. This randomization method guarantees an allocation concealment format, meaning that the person responsible for the task will be unaware of the next group allocation. Due to the protocol differences, it is not feasible to blind the participants or treating clinicians to the condition. Nonetheless, the research team member performing data collection and analysis will be blinded to the group allocation, whether control or experimental.

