**FIGURE 2 F2:**
[figure not shown]
Application of kinesiology taping.

Team members will customize an I-shaped tape and a reverse V-shaped tape. The hyoid bone and thyroid cartilage will be marked with a pen. First, an I-shaped tape will be applied by pulling it downward to the level of the thyroid notch to wrap around the thyroid cartilage and attach it to the sternum. Second, the team members will attach a reverse V-shaped tape from the hyoid bone to the superior medial surface of the clavicle on both sides. Finally, they will cover the hyolaryngeal complex horizontally to restrict its movement throughout swallowing, ensuring the tape is securely attached.

Tapes will be replaced daily with an application at approximately 70%–80% tension.

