### 3.1 Strengths and limitations

Although this randomized controlled trial is the pioneer in exploring the effectiveness of kinesiology taping for treating dysphagia in survivors of brain tumors after undergoing neurosurgical intervention, we have built the protocol based on previous work examining the effectiveness of kinesiology taping on stroke survivors, thus expecting to achieve positive outcomes. In addition, the chosen outcome measures represent those most practically implemented in the clinical settings.

To ensure this randomized controlled trial was designed following trial standards, we used the SPIRIT statement, which is widely endorsed as an international standard for trial protocols, to enhance the quality, transparency, and completeness of trial protocols, which can help to improve the overall reliability and validity of this clinical trial results. Nonetheless, it should be noted that this trial has limitations. First, blinding is essential to minimize bias that can affect study outcomes. In this trial, it is not feasible to blind participants or team members who will implement the intervention. However, to minimize data collection and analysis bias, the research team members responsible for these tasks will be blinded to the treatment allocation, whether the participant received the intervention or the placebo/control. Second, there is no uniform standard care treatment for people with dysphagia in Portugal. For this reason, team members will perform the usual treatment in the Neurosurgery Inpatient Unit, bearing in mind that the time and periodicity of the intervention applied in this trial are possibly more prolonged than the time of rehabilitation care practiced in other similar units. Third, we expect some participants to not complete the intervention due to being transferred to other units or facilities (e.g., rehabilitation units). To minimize the impact of this occurrence on the research results, we assume a dropout rate of 15% when calculating the study’s sample size.

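### Section 2.3 removes randomised participants from the study for pneumonia or instability, so T1 data are lost for a reason tied to swallowing

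*Protocol article*

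**What the plan says.** Section 2.3 of the protocol article deals with pneumonia and instability twice. Exclusion (d) covers people who have "developed pneumonia or unstable medical conditions during the study". The closing paragraph of the section then says: "Any subjects who develop pneumonia or other unstable medical conditions at any point will be removed from the study". The rule speaks of leaving the study, not of stopping the taping or the swallowing sessions.

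Section 2.5 fixes the order of events: "Following baseline assessments, participants will be split into two groups". It also says that participants and treating clinicians cannot be blinded. Section 2.8 sets two assessments of the primary outcomes (PAS from FEES, GUSS, DHI, FOIS): T0 at baseline, and T1 up to 24 hours after the final session. The same section lists adverse events during the intervention as a secondary domain, to be recorded in the case report form. Section 2.9 names a repeated measures ANOVA.

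On losses, Section 2.4 allows 15% dropout. Section 3.1 gives transfer to other units as the expected reason, and continues: "To minimize the impact of this occurrence on the research results, we assume a dropout rate of 15" per cent.

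**The concern.** An event that can only occur after allocation is being used to decide who stays in the trial. The protocol itself ties that event to the condition under study: the Introduction says that dysphagia "increases the risk of aspiration pneumonia". Section 2.6 (text under Figure 2) says that the tape covers the hyolaryngeal complex "to restrict its movement throughout swallowing", so an influence of treatment on aspiration in either direction cannot be ruled out. What counts as an unstable condition is not defined in the article, and the clinicians who would recognise it know the allocation.

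At stake is the randomised comparison. If taping helps, more of the poorly swallowing controls may leave and the benefit looks smaller. If taping harms, more of the harmed may leave the taping arm and the harm looks smaller. Enlarging the sample restores precision but does not correct selection. An analysis plan can choose how to handle missing values, but it cannot recover T1 assessments that the protocol stops collecting.

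**Working it through.** **1. The plan's own allowance.** 34 / (1 − 0.15) = 40 per group, 80 in total, as Section 2.4 states. This checks the inflation step only. It concerns the number of participants, not which ones are lost.

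**2. Is the exclusion after randomisation, and related to outcome?** Section 2.5 puts allocation after baseline, and Section 2.3 applies the rule at any point, so events during the intervention fall after allocation. The Introduction gives the link to the outcome for pneumonia. With T1 the only post-baseline measurement, a participant removed before T1 has no outcome value.

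**3. Size when treatment has an effect.** The documents give no pneumonia rate and no relation between pneumonia and T1 score, so every input here is an assumption. Let y be T1 severity (higher is worse, SD 1), with mean 0 in control and −0.69 (benefit) or +0.5 (harm) with taping. The removal probability is expit(a + b·y), with the same a and b in both arms. The mean among those kept is E[y(1 − p(y))] / E[1 − p(y)], and the estimate is the difference between arms.

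| (a, b) | Removed, control | Removed, taping (benefit) | 0.69 SD estimated as | Removed, taping (harm) | 0.5 SD harm appears as |
|---|---|---|---|---|---|
| (−3.5, 1) | 4.5% | 2.4% | 0.67 | 7% | 0.48 |
| (−2.5, 0.5) | 8% | 6% | 0.68 | 10% | 0.49 |
| (−2.5, 1.5) | 14% | 6% | 0.61 | 22% | 0.41 |
| (−2, 2) | 22% | 10% | 0.55 | 35% | 0.36 |

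The shortfall in the benefit runs from (0.69 − 0.68)/0.69, about 2% before rounding of the estimate, to (0.69 − 0.55)/0.69, about 21%. The upper end needs both a high pneumonia rate and a steep link to severity.

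**4. Size when treatment has no effect on y.** In this second model, removal depends on a normal liability correlated with y at 0.3, 0.5 or 0.8.

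- Equal removal (5% v 5%, 15% v 15%): bias within 0.001 SD of zero.
- 15% v 5%: a spurious difference of 0.05, 0.08 and 0.13 SD.
- 20% v 10%: 0.05, 0.08 and 0.12 SD.
- Upper limit for 15% v 5%, where removal takes exactly the worst scores: the mean shift is φ(z)/(1 − p), giving 0.274 − 0.109 = about 0.17 SD.

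In the unequal cases the difference favours the arm with more removals. As a guide to error rates, take a difference of two means with 40 per arm and a shift of 0.10 SD: 0.10/√(2/40) = 0.447, and Φ(0.447 − 1.96) + Φ(−0.447 − 1.96) = 0.073 in place of 0.05. A shift of 0.15 SD gives 0.103.

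**5. Can the harm be counted by arm?** Adverse events are documented (Section 2.8). Pneumonia is not a named outcome, however; it is also an exclusion reason, and the secondary outcomes are evaluated at T1, which a removed participant does not reach. A pneumonia should therefore appear in the case report form, but nothing shown ensures that it is tabulated against the arm to which the person was randomised.

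**The case against.** The strongest reply has five parts.

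- **Harm is not hidden.** A reader might infer that the rule conceals pneumonia. Section 2.8 does not support that: adverse events during the intervention are recorded, and a pneumonia that triggers removal falls within that period. Tabulation is often left to an analysis plan. This stands. What remains is that the event doubles as an exclusion reason, so its count by arm is not secured.
- **The worst outcomes are not shown to be the ones lost.** A reader might infer that removal deletes the poorest swallowers. For pneumonia that is a reasonable inference from the Introduction; for other unstable conditions after brain surgery it need not hold. This stands as a limit.
- **The losses may already be budgeted.** A reader might infer that removals come on top of the 15%. Section 2.4 gives a general rate and Section 3.1 names transfers as the expected cause; neither says that removals are outside it. This stands, and no shortfall in numbers is claimed here.
- **The figures are assumed.** This is correct. Mild inputs give a bias of about 2%, and the same mechanism with no effect gives none.
- **Missing-data handling belongs in the analysis plan, and this is a pilot.** The article is silent on missing data and that silence is no fault. But the removal rule is stated outright and determines what is collected. The Abstract and Section 1 also present the trial as assessing the effect of taping, so pilot status does not make the comparison unimportant.

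**Conclusion.** The concern holds in limited form. Section 2.3 prescribes exclusion after randomisation for an event that the protocol itself relates to dysphagia. Clinicians are unblinded and there is a single post-baseline assessment. The resulting loss of T1 data is likely to be informative, at least for pneumonia, and may be unequal between arms.

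Neither the size nor the direction of the bias can be known from the documents. Under assumed control removal of about 5% to 22%, a 0.69-SD benefit would be underestimated by about 2% to 21% (0.55 to 0.68 SD). A 0.5-SD harm would appear as about 0.36 to 0.49 SD, with about 7% to 35% removed from the taping arm. If taping has no effect and removal works identically in both arms, the bias is zero, although the people analysed are then no longer all those randomised. The documents do not support a claim that the trial will reach a wrong answer or that pneumonia goes unrecorded. The rule should be changed before enrolment because uncollected T1 data cannot be recovered.

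**What to change.** - Take the in-study event out of exclusion (d), so that eligibility does not depend on what happens after allocation.
- Reword the removal sentence so that stopping the intervention is separate from leaving the study. Stopping and care remain decisions of the treating team; no clinical rule is proposed here.
- Keep these participants in follow-up and collect T1 at its planned time where feasible. FOIS and DHI need no endoscopy and are the minimum. Because T1 is anchored to the final session, state what the planned time means for someone who stops early. Moving T1 forward to the day of transfer or removal would not match Section 2.8 and would mix lengths of exposure.
- Analyse all participants as randomised, with a sensitivity analysis that gives those with pneumonia and no T1 the worst rank. This can sit in the analysis plan.
- Report pneumonia by randomised arm.

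The cost is a change of protocol wording and a few T1 assessments that will be harder to obtain. No additional participants are needed.

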### 2.4 Sample size calculation

A repeated measures ANOVA with within-between interactions was chosen to evaluate the impact of the treatment on each group relative to their baseline. To achieve 80% power, with an alpha of 0.05, a medium effect size of 0.25, two groups, two measurements per group, a correlation of 0.5 among repeated measures, and a non-sphericity correction of 1, we used GPower v.3.1 (24) to calculate the required sample size, which resulted in 34 subjects per group. Considering a 15% dropout rate, the final sample will consist of 80 individuals (*n* = 40 per group) who meet the inclusion criteria.

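### The inputs in section 2.4 require 34 participants in total, not 34 per group, so the stated 80% power, effect size and sample size do not fit together

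*Protocol article*

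**What the plan says.** Section 2.4 names the test ("A repeated measures ANOVA with within-between interactions was chosen") and then gives its inputs: "To achieve 80% power, with an alpha of 0.05, a medium effect size of 0.25, two groups, two measurements per group", with "a correlation of 0.5 among repeated measures" and a non-sphericity correction of 1, run in G*Power 3.1. It reports the outcome as a calculation "which resulted in 34 subjects per group". It then allows for 15% dropout and arrives at 80 participants, 40 per group. The abstract gives a different recruitment figure, 62. Section 2.1 sets 1:1 allocation.

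**The concern.** Because every input is stated, the calculation can be repeated exactly. When it is, 34 comes out as the number for both groups together. The power quoted then does not belong to the sample planned. A reader who takes section 2.4 at face value would believe that 68 evaluable participants are what an effect of f = 0.25 needs for 80% power, when half that number is enough. The plan's justification for its size, and any later statement about what the trial could detect, would rest on a figure that its own assumptions do not produce.

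**Working it through.** **Inputs, all from section 2.4.** Interaction test; f = 0.25 (read as Cohen's f, the effect size this software uses for this test); alpha 0.05; k = 2 groups; m = 2 measurements; correlation rho = 0.5; epsilon = 1; target power 0.80; dropout 15%.

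**Formula.** For the within-between interaction, with N the total sample size:

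- lambda = N × f² × m × epsilon / (1 − rho)
- df1 = (k − 1)(m − 1) = 1; df2 = (N − k)(m − 1) = N − 2

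With the stated inputs, lambda = N × 0.0625 × 2 / 0.5 = 0.25 N.

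**Attempt to reproduce the plan's figure.**

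| Total N | Per group | lambda | Power, f = 0.25 |
|---|---|---|---|
| 32 | 16 | 8.0 | 0.781 |
| 34 | 17 | 8.5 | 0.807 |
| 68 | 34 | 17.0 | 0.982 |

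The smallest balanced total that reaches 80% is 34. Simulating a two-sample t-test on change scores (40,000 runs) gives 0.806 at N = 34 and 0.982 at N = 68.

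**Other readings of the calculation (total N for 80% power).**

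- Within-factor test: 34
- Between-factor test: 98
- Noncentrality without the m/(1 − rho) factor: 128 with f²N, 130 with f²(N − 2)
- Alpha 0.025: 42; alpha 0.0125: 48
- Three measurements: 28
- Correlation 0: 66

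None gives 68. Only a correlation of 0 comes near, and it contradicts the stated 0.5.

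**Dropout.** This step is sound: 34/0.85 = 40 and 68/0.85 = 80. Applied to the correct total, it gives 40 participants in all, 20 per group.

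**What f = 0.25 means here.** In a two-by-two interaction each cell departs from additivity by a quarter of the between-group difference in change, so that difference is 4f = 4 × 0.25 = 1.0 SD. The SD of change is SD × √(2(1 − 0.5)) = SD, so this is 1.0 SD on either scale. As a check, a t-test on change with a 1.0-SD difference and 17 per group has squared noncentrality 17/2 × 1.0² = 8.5, equal to lambda above.

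**What each stated size delivers after 15% loss.** The 0.5-SD column is f = 0.5/4 = 0.125.

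| Randomised | Evaluable | Power, f = 0.25 (1.0 SD) | f at 80% power | Difference in change at 80% power | Power, 0.5 SD |
|---|---|---|---|---|---|
| 80 (section 2.4) | 68 | 0.982 | 0.172 | 4 × 0.172 = 0.69 SD | 0.53 |
| 62 (abstract) | 62 × 0.85 = 52.7, taken as 52 | 0.942 | 0.198 | 4 × 0.198 = 0.79 SD | 0.42 |

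These figures are for one outcome at alpha 0.05.

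**The case against.** The strongest reply is that the mistake is harmless. It errs on the safe side: for the effect the plan names, the trial has more power than claimed, about 98% with 68 evaluable and still about 94% with 52. The study is also described as a pilot. All of that stands, and it limits the consequence. It does not make the paragraph right, because a calculation published with all its inputs should reproduce, and this one presents 80 as what those inputs require.

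A reader might go further and infer that the trial is underpowered, or that a null result would wrongly be taken to exclude a medium effect with 80% power. The document does not support that. It specifies "a medium effect size of 0.25" on the f scale and nowhere mentions 0.5 SD or any standardised mean difference. Against f = 0.25 as written, a null result would be more informative than 80% power implies. The 53% and 42% figures apply only if a 0.5-SD difference is of interest, which is an assumption brought from outside the plan. They follow from how the effect is expressed, not from confusing a total with a per-group number.

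The numerical target is fully specified, so the adjective attached to it is a matter of clarity and not an arithmetic error. Finally, the cause is inferred: the exact match at 34 makes a misread total likely, but the document does not show it.

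**Conclusion.** The sample size statement is wrong as written. The listed inputs need 34 in total and 40 after dropout, half of the 68 and 80 that section 2.4 derives from them. The stated 80% is about 98% at the planned evaluable number. The direction is conservative for the stated effect, so the trial is not short of patients by its own reckoning.

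The conclusion rests on reading 0.25 as Cohen's f and on the software's default noncentrality for this test; none of the alternatives tried on the stated inputs recovers 34 per group. The delivered-power figures also assume 15% loss and equal groups. They depend on which recruitment figure is the real one, since the abstract and section 2.4 disagree.

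**What to change.** Rewrite section 2.4 in three steps.

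1. State that the listed inputs require 34 participants in total (17 per group), or 40 in total after 15% dropout.
2. Settle whether 80 or 62 will be randomised, make the abstract and section 2.4 agree, and justify that number by what it delivers. For 80 randomised and 68 evaluable: about 98% power for f = 0.25, and 80% power for f = 0.17 (a 0.69-SD difference in change). For 62 randomised and about 52 evaluable: about 94% for f = 0.25, and 80% for f = 0.20 (0.79 SD).
3. Express the target effect as a between-group difference in change, in SD or scale points, in place of the adjective. If the investigators regard 0.5 SD as worth detecting, they should say so and report the corresponding power, about 53% with 68 evaluable or 42% with 52.

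The cost is the rewording of one paragraph and the alignment of one figure in the abstract. The correction calls for no additional recruitment.
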